1. Exclusion criteria (inpatients)
2. Those whose diabetic retinopathy condition is not stable
3. People with diabetic nephropathy stage 4 or higher
4. Persons with untreated ischemic heart disease
5. Epilepsy patients
6. Subjects with a history of hypersensitivity to the ingredients of the drug used in this study
7. Pregnant women, lactating women, or those who may be pregnant
8. Any other person who is judged by the research director or co-researcher to be inappropriate as a research subject.

Exclusion criteria (volunteer)

1. Those who have been diagnosed with a disease that causes hypoglycemia (blood glucose less than 60 mg/dl) in the past.
2. Subjects with a history of hypersensitivity to the ingredients of the drug used in this study
3. Pregnant women, lactating women, or those who may be pregnant.
4. Those under 30 years of age and with a BMI of less than 18.5 kg/㎡
5. Those with untreated ischemic heart disease
6. Epilepsy patients
7. Any other person who is judged by the research director or co-researcher to be inappropriate as a research subject.

4) How to recruit volunteers

The attached recruitment materials will be posted inside Hokkaido University and volunteers will be solicited.

5. Research method

(1) Type and design of research

Confirmatory clinical trial

(2) Exam outline

After completing all of Study 1, statistically analyze the clinical data obtained in Study 1, and if the usefulness of the simple insulin tolerance test is suggested, conduct Study 2 to verify the reproducibility of the simple insulin tolerance test. Inpatients will participate in either Study 1 or Study 2. Volunteers will be able to participate in both studies.

<Research 1>

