14. Cancellation, interruption, or termination of research

(1) Termination or suspension

The co-researcher will consider whether to continue conducting the research if any of the following apply.

① When they become aware of matters related to safety and efficacy and other important information.

②When it is judged that it is difficult to recruit research subjects and it will be extremely difficult to reach the expected number of cases.

③When the purpose of the research is achieved before the planned number of cases or the planned period is reached.

④When the screening committee has given instructions to change the implementation plan, and it is determined that it is difficult to accept the instructions.

The research director will discontinue the research if the review committee recommends or instructs it to be discontinued. In addition, when a decision is made to discontinue or suspend research, promptly report the reason in writing to the director of the research institution.

(2) Completion of research

Upon completion of the research, the research director will promptly submit a research completion report to the head of the research institution.

15. Research implementation period

Implementation permission date - March 31, 2018

16. Target number of cases, basis for setting it, and statistical analysis method

(1) Target number of cases and basis for setting it

<Research 1> 24 cases (7 volunteers, 17 diabetic patients) [Based for setting] Assuming a correlation coefficient of 0.6, setting a power of 80% and a significance level of 5%, n = 19 cases will be required. The sample was set at n=24, assuming that 20% of cases would drop out.

<Research 2> 11 cases (6 volunteers, 5 diabetic patients) [Based for setting] Assuming that the expected intraclass correlation coefficient for two measurements is 0.8 and the intraclass correlation coefficient for the null hypothesis is 0.1, the required number of subjects is 9 with a significance level of 5% and a power of 80%6⁾. The sample was set at n=11, assuming that 20% of cases would drop out.

(2) Statistical analysis method

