For study 1, Pearson's correlation coefficient was calculated for the correlation between Kitt (SITT) calculated from the SITT results and Kitt (i.m.) calculated from the simple insulin tolerance test, and a correlation coefficient of 0 was set as the null hypothesis. Perform a two-tailed test. For estimation of the calibration straight line, orthogonal regression with a variance ratio of 1 is performed.

For Study 2, Fisher's Z transformation was performed on the intraclass correlation coefficient, and the null hypothesis was tested at 2.5% on one side6⁾. Other statistical analyzes will be described in the statistical analysis plan.

17. Consideration for the human rights of research subjects

All researchers in this research must comply with the Declaration of Helsinki (revised in October 2013) and the Ethical Guidelines for Medical Research Involving Human Subjects (Ministry of Education, Culture, Sports, Science and Technology/Ministry of Health, Labor and Welfare Notification No. 3 of 2014).

18. Handling of personal information

When handling samples and information related to research implementation, sufficient consideration should be given to protecting the confidentiality of research subjects by assigning numbers unrelated to the personal information of the research subjects and managing them in a linkable and anonymized manner. The research director will supervise that the anonymization correspondence table is stored in strict confidence. In addition, when research directors and others publish information obtained through this research, they will ensure that it does not include information that could identify research subjects.

19. How to obtain consent

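### Study 2 is meant to verify reproducibility, but the only criterion the protocol fixes is rejection of an ICC of 0.1, which supports no more than an ICC above 0.1.

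*Protocol*

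**What the plan says.** Section 5(1) of the Protocol gives the design as "Confirmatory clinical trial". Section 5(2) makes Study 2 conditional on Study 1 suggesting that the simple test is useful, and then states the aim: "conduct Study 2 to verify the reproducibility of the simple insulin tolerance test". Under <Research 2> in the same section, the two repeat tests, on different days within a 3-day window, are there to confirm reproducibility, in patients and in volunteers.

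Section 16(1) gives the sizing. "Assuming that the expected intraclass correlation coefficient for two measurements is 0.8", and "the intraclass correlation coefficient for the null hypothesis is 0.1"; from these, "the required number of subjects is 9 with a significance level of 5% and a power of 80" per cent. Enrolment is 11 (6 volunteers and 5 diabetic patients): "The sample was set at n=11, assuming that 20% of cases would drop out".

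Section 16(2) fixes one analysis for Study 2. The ICC is Fisher Z-transformed and "the null hypothesis was tested at 2.5% on one side". Other analyses are left to the statistical analysis plan. The Protocol gives no reason for 0.1 beyond a literature reference, no minimum acceptable ICC and no target precision.

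**The concern.** With two measurements per subject, the ICC is the share of total variance that lies between subjects. At an ICC of 0.1, 10% is between subjects and 90% is within-subject variation. Rejecting that value shows that repeat tests on one person are not close to unrelated. It does not show that the repeat result is close enough to the first for the test to be called reproducible.

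The aim and the criterion are therefore at different levels: the aim is verification, while the null lies near the bottom of the scale. What is at stake is the sentence the study can support at the end. If the criterion is met, the data may still be compatible with an ICC little above 0.1, and even a good observed value leaves a wide interval.

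**Working it through.** **Inputs (Section 16).** Null ICC 0.1; expected ICC 0.8; k = 2 measurements; one-sided 2.5%; power 80%; 9 evaluable, 11 enrolled.

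**Step 1: reproduce the Protocol's 9.** A standard approximation (Walter-Eliasziw-Donner) is n = 1 + 2k(zα + zβ)² / [(k − 1)(ln C₀)²], with C₀ = [1 + k·0.1/0.9] / [1 + k·0.8/0.2].
- C₀ = 1.2222 / 9 = 0.1358; (ln C₀)² = 3.986.
- (1.960 + 0.842)² = 7.849.
- n = 1 + 4 × 7.849 / 3.986 = 8.88, rounded up to 9.

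Fisher's Z with variance 1/(n − 1.5) gives 9.38. At n = 9, power is 78.9% by the exact F test and 78.1% by Fisher's Z. A one-sided 5% test would need only 7.2 to 7.7. So the stated 9 is right for its inputs at one-sided 2.5%.

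**Step 2: smallest observed ICC that is significant.** For a one-way ICC with two measurements, ICC = (F − 1)/(F + 1), and the null corresponds to a ratio of 1.1/0.9 = 1.2222.
- n = 9: critical F = 1.2222 × F.975(8, 9) = 1.2222 × 4.102 = 5.014, so ICC = 4.014/6.014 = 0.667.
- n = 11: critical F = 1.2222 × F.975(10, 11) = 1.2222 × 3.526 = 4.309, so ICC = 3.309/5.309 = 0.623.

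Fisher's Z gives 0.673 and 0.627, practically the same.

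**Step 3: 95% intervals.** Lower limit from F/F.975(n − 1, n), upper from F × F.975(n, n − 1), each converted by (x − 1)/(x + 1). An observed ICC of 0.8 corresponds to F = 1.8/0.2 = 9. For n = 9 the lower limit is 9/4.102 = 2.194, which converts to 1.194/3.194 = 0.37.

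| Observed ICC | n = 9 | n = 11 |
|---|---|---|
| Just significant (0.667; 0.623) | 0.10 to 0.91 | 0.10 to 0.88 |
| 0.8, as planned | 0.37 to 0.95 | 0.44 to 0.94 |

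**Step 4: power at n = 9 if the true ICC is 0.8.** The Protocol names no other null, so 0.5 and 0.6 are illustrative.

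| Null ICC | Power |
|---|---|
| 0.1 (Protocol) | 79% |
| 0.5 | 32% |
| 0.6 | 19-20% |

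**Step 5: how often the test against 0.1 is significant (exact F).**

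| True ICC | n = 9 | n = 11 |
|---|---|---|
| 0.3 | 8% | 9% |
| 0.4 | 14% | 16% |
| 0.5 | 23% | 28% |
| 0.6 | 37% | 45% |

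**The case against.** Several points on the other side stand.

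- A reader might infer that the Protocol will declare the test reproducible once the null is rejected. It never says so. Section 16 contains no Study 2 conclusion, and the research background states the aim more softly, as an evaluation. The text also reads as a translation, so one verb should not carry too much weight. What remains is that no other criterion is fixed for an aim worded as verification in one place and confirmation in another.
- A reader might infer that a poor test would pass easily. It would not. An observed ICC of about 0.62 to 0.67 is needed, and a true ICC of 0.3 gives significance only 8-9% of the time. An interval that touches 0.1 is the boundary case, as it is for any test that just reaches significance. Nor is a pass at a true ICC of 0.6 shown to be wrong, since no minimum acceptable ICC is set.
- It would be too strong to say that the design cannot reject a demanding ICC. It has low power to do so.
- The ICC interval and the within-subject SD may already be in the statistical analysis plan, which is not at hand. Their absence from the Protocol is not the fault. But the aim, the null and the number of subjects are set in the Protocol, and no analysis plan can add precision that 9 to 11 subjects do not give.
- Section 11 has Study 2 results fed into guidance whatever the ICC turns out to be. The choice of null is therefore not shown to change any participant's management.
- The primary endpoint in Section 9 is the Study 1 correlation, which this point does not touch.

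**Conclusion.** The point holds as a mismatch between aim and criterion. The sample-size arithmetic is sound. The weakness is that a null of 0.1 supports only a claim of ICC above 0.1, and that 9 to 11 subjects cannot narrow the estimate enough to carry the word verify: at the planned ICC of 0.8 the lower limit is 0.37 (n=9) or 0.44 (n=11). The study reaches about 80% power at this size because the null is so low.

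The figures assume a one-way ICC, two measurements per subject, normally distributed Kitt and all subjects treated as one sample. The Protocol's Fisher Z test and the exact F test agree closely. Pooling volunteers with patients tends to raise between-subject variance and with it the ICC, which would make 0.1 easier to exceed without any better repeatability.

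**What to change.** Keep the sample size, the null and the test.

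1. In Section 16, add that rejection shows only that the ICC exceeds 0.1. Add that the reproducibility conclusion rests on the ICC with its 95% CI, read at the lower limit, and on the within-subject SD and CV of Kitt from the duplicate tests. If the statistical analysis plan already contains these estimates, refer to them.
2. In Section 5(2), including the text under <Research 2>, replace verifying and confirming reproducibility with obtaining a preliminary estimate of it.

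The cost is wording and a few estimates from data already planned, with no extra subjects. The downside is a weaker claim. Retaining the stronger one would need a larger study: with an expected ICC of 0.8 and an illustrative null of 0.5, the same one-sided 2.5% test at 80% power needs 28 evaluable subjects, or 28/0.8 = 35 enrolled with 20% dropout.

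### Study 2's enrolment of 11 falls just short of the stated 20% dropout allowance on the 9 required; power stays close to 80%

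*Protocol*

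**What the plan says.** Protocol section 16(1), Research 2, bases the sample size on an intraclass correlation (ICC) for two measurements: "Assuming that the expected intraclass correlation coefficient for two measurements is 0.8", and "the intraclass correlation coefficient for the null hypothesis is 0.1". From these it concludes that "the required number of subjects is 9 with a significance level of 5% and a power of 80"%. It then enrols more to allow for losses: "The sample was set at n=11, assuming that 20% of cases would drop out". The 11 are made up of 6 volunteers and 5 diabetic patients.

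Section 16(2) plans a Fisher Z test of the ICC, in which "the null hypothesis was tested at 2.5% on one side".

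For Study 1, section 16(1) goes from 19 required to 24 enrolled in the same words: "The sample was set at n=24, assuming that 20% of cases would drop out". Neither study is given an inflation formula or a rounding rule.

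**The concern.** A dropout allowance should leave the required number after the assumed losses. Study 1's target does this and Study 2's does not, although both sit in the same section and assume the same 20%. The required 9 is itself a rounded-up minimum with almost nothing to spare, so any shortfall takes the expected power below the stated 80%. Study 2 is the reproducibility part of a trial that section 5(1) labels confirmatory, so its sample-size statement should agree with its own figures. What is at stake is the accuracy of that statement and, to a small degree, the power it claims.

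**Working it through.** **Inputs** (Protocol section 16): ICC 0.8 under the alternative and 0.1 under the null, k = 2 measurements, one-sided 2.5% (z = 1.960), power 80% (z = 0.842), 9 required, 11 enrolled, 20% dropout. Study 1: 19 required, 24 enrolled, 20% dropout.

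**1. Reproducing the 9.** The usual ICC sample-size formula on the log scale is n = 1 + 2k(z_a + z_b)^2 / [(k - 1)(ln C)^2], where C is the ratio of (1 + (k - 1)ICC)/(1 - ICC) under the two hypotheses.
- Alternative: 1.8/0.2 = 9. Null: 1.1/0.9 = 1.222. C = 7.364 and ln C = 1.997.
- n = 1 + 4 x (1.960 + 0.842)^2 / 1.997^2 = 8.88, so 9. The plan's figure is reproduced.
- At one-sided 5% the same formula gives 7.2, so 8. The 9 therefore matches the 2.5% one-sided test in section 16(2).

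**2. Dropout allowance.**

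| | Required | Required/0.8 | Required x 1.2 | Stated n | Stated n x 0.8 |
|---|---|---|---|---|---|
| Study 1 | 19 | 23.75 | 22.8 | 24 | 19.2 |
| Study 2 | 9 | 11.25 | 10.8 | 11 | 8.8 |

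Study 1 keeps at least 19. Study 2 is 0.2 of a subject below 9, and 0.08 below the unrounded 8.88. In whole subjects, 11 tolerates 2 losses: 2/11 = 18.2%.

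**3. Power, one-sided 2.5%.** Three calculations:
- (a) the formula above inverted: Phi(sqrt((n - 1)/4) x 1.997 - 1.960);
- (b) Fisher Z with variance 1/(n - 3/2): Phi(sqrt(n - 1.5) x 0.998 - 1.960), where 0.998 = atanh 0.8 - atanh 0.1;
- (c) exact F with n - 1 and n degrees of freedom.

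| Completers | (a) | (b) | (c) |
|---|---|---|---|
| 9 (2 lost of 11) | 80.6% | 78.1% | 78.9% |
| 8.8 (20% of 11 lost, on average) | 79.6% | 77.0% | 77.9% |
| 8 (3 lost of 11, 27.3%) | 75.2% | 72.1% | 73.2% |
| 11 (none lost) | 88.4% | 86.8% | 87.2% |

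Averaged over binomial 20% dropout:

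| Enrolled | (a) | (b) | (c) | Chance of at least 9 completers |
|---|---|---|---|---|
| 11 | 78.7% | 75.9% | 76.9% | 62% |
| 12 | 82.4% | 80.1% | 80.8% | 79% |

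**The case against.** The best defence is that this is only rounding. Dividing by 0.8 and rounding to the nearest integer gives both stated targets (23.75 to 24, 11.25 to 11). The nearest whole-number reading of 20% of 11 is 2 losses, which leaves exactly 9 and 80.6% power by the formula that reproduces the plan. One subject is well inside the uncertainty of the assumed ICCs. Participation is short, with two tests within 3 days, and the primary endpoint in section 9(1) is the Study 1 correlation.

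Most of this stands, and it limits the point to a minor one. It does not make the sentence correct: a minimum sample size has to be rounded up, and 20% of 11 does not leave 9.

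Three stronger readings are tempting, and the document does not support them:
- **That the plan used a wrong formula, multiplying by 1.2.** This fits 11, but so does rounding 11.25 to the nearest integer. The Protocol shows neither route.
- **That power falls to 72-75%.** This needs 8 completers, which is 3 losses of 11 or 27%, above the assumed rate.
- **That the 78% from Fisher Z at 9 completers shows the harm of the dropout allowance.** That gap is there with all 9 present. It comes from using a different approximation from the one that reproduces the 9.

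**Conclusion.** The point holds in a limited form. The stated 11 does not cover a 20% loss from the required 9, while Study 1's 24 does cover its own. The shortfall is 0.2 of an expected completer. At the assumed dropout, power is 79.6% at the expected number, or 78.7% averaged over random dropout, by the formula that reproduces the 9. It is about 76-78% by Fisher Z with n - 3/2 or exact F. A reader might infer that the study is materially underpowered, but these figures do not show that. Severity is minor.

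The result assumes that the 9 came from the formula in step 1. The Protocol attributes it to a reference that is not at hand, but the match at 8.88 is close. The averaged figures also assume that subjects drop out independently, each with probability 20%.

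**What to change.** Correct one sentence in section 16(1), Research 2, in either of two ways:
- state that 11 allows for 2 losses (about 18%) and leaves the 9 required; or
- keep the 20% allowance and state that the expected power is just under 80% (about 79% by the formula that gives the 9).

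Neither adds a subject or changes the analysis. The restated sentence should not pair 20% dropout with 8 completers, because 8 of 11 means a 27% loss. If the sponsor prefers to keep both 20% and 80% as stated, 12 is the smallest enrolment that does so. That costs one more subject and a revised split between volunteers and patients. Stating the inflation and rounding rule once for both studies would settle how the figures were reached.
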